### Randomization and blinding

Each number from 1 to 250 will be randomly pr-assigned to either the control or experimental group by a random number generator, with 125 numbers assigned to each group. These numbers will be assigned in sequential order to participants as they are enrolled. The staff that generate the randomization list, and prepare and label each intervention/control jar with study numbers will do so prior to delivery of the interventions to the field and those staff will have no further involvement in the study. A designated field team member not involved in sample collection or anthropometric measurements will distribute the jars to the study participants. These field researchers will be trained in anthropometry, study protocols, the assessment of acute malnutrition, and good clinical research practices by the senior physicians and investigators. Researchers involved in the collection of samples and analysis of data will not directly handle, distribute, or view the intervention flours, nor will any of the paperwork they handle include information about the assigned intervention group. Care will be taken to ensure that the experimental and control powders look as similar as possible, but there are very subtle color, particulate, and texture differences between the two. Although caregivers will not be told to which group their children are randomized, it will be possible for them to differentiate the two different powders being used in the study should they undertake a very close comparison with another subject’s flour.

### Study participation

On the enrollment date, children will be screened for eligibility via clinical anthropometric measurements and a short questionnaire regarding recent illnesses. Children without any exclusion criteria will be given a study number, and will complete the lactulose absorption test, stool collection, and blood draw after consent is provided. HSAs will work with caregivers to complete a questionnaire that includes basic sociodemographic, economic, sanitary, and dietary data specific to lactoferrin- and lysozyme-containing foods, along with an account of recent illnesses in the previous 7 days. After completion of sample collection, each participant will receive a 4-week supply of the intervention corresponding to their assigned study number. Local staff will then educate caregivers on how to prepare and feed the interventions to the children. Recruitment of trial participants began in October 2016 and the trial is ongoing.

At subsequent monthly visits, study participants will return for anthropometric measurements, with or without sample collections. Questionnaires that primarily detail recent illnesses, medical visits, diet, and compliance by asking the caretaker how many days of the intervention were missed will be completed. The complete schedule of study visits, testing, and distribution of interventions is provided in the SPIRIT format in Fig. 2.

**Fig. 2 Fig2:**
[figure not shown]
SPIRIT figure: study participation schedule for subjects

### Anthropometry

Anthropometric data will be obtained at every visit. Weight will be assessed to the nearest 5 g using standard digital scales (Seca 334, Chino, California, USA) and height will be measured to the nearest 0.1 cm using standard rigid height boards (Seca 417, Chino, California, USA). MUAC will be measured to the nearest 0.1 cm using standard flexible tape inserts (TALC, St. Albans, UK). Each child will be assessed for edema indicative of kwashiorkor by pressing on the dorsum of the left foot. The field research staff supervising anthropometry have been working in similar field sites and study conditions and trials for 5–15 years each, and will ensure that any junior research staff are fully trained and vetted prior to initiating the study. A random sampling of measurements each day will also be conducted by at least two field staff in order to verify that consistent and accurate measurements are being taken and corrective measures initiated as soon as any inaccuracies are identified.

Anthropometric *Z* scores will be calculated based on the 2006 World Health Organization (WHO) Multicentre Growth Reference Survey [50]. During both enrollment and subsequent visits, any child with a weight-for-height *Z* score less than –2, MUAC less than 12.5 cm, or presence of pitting edema will be classified as acutely malnourished and excluded from the study. Children excluded due to acute malnutrition will then be enrolled in supplementary or therapeutic feeding programs and receive usual medical care according to standard protocols [51–53].

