**Methods/design:**

A prospective randomized placebo-controlled parallel-group randomized controlled trial will be conducted to determine if a daily supplement of lactoferrin and lysozyme, two important proteins found in breast milk, can decrease the burden of EED and stunting in rural Malawian children aged 12–23 months old. The intervention and control groups will have a sample size of 86 subjects each. All field and laboratory researchers will be blinded to the assigned intervention group, as will the subjects and their caregivers. The percentage of ingested lactulose excreted in the urine (Δ%L) after 4 h will be used as the biomarker for EED and linear growth as the measure of chronic malnutrition (stunting). The primary outcomes of interest will be change in Δ%L from baseline to 8 weeks and to 16 weeks. Intention-to-treat analyses will be used.

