### Outcomes and sample size

The primary outcomes of interest will be improvement of a major biomarker of EED, the percent of ingested lactulose excreted in the urine (Δ%L), from baseline to 8 weeks and to 16 weeks. Linear growth has been shown to best correlate with this component of the traditional dual-sugar absorption test [42]. The enrollment goal will be at least 86 subjects in each of two equally sized intervention or control groups. This sample size was chosen to detect a decrease of 0.05% in Δ%L between the two groups (considered to be a clinically significant improvement in gut barrier function) with an alpha value of 5% and 90% power. This assumes that urinary lactulose measurements will be distributed similarly to prior studies that showed that more than 80% of apparently healthy rural Malawian children had EED. Additional children will be enrolled to account for children who drop out or are excluded during the course of the study, as well as for some children who will not have a satisfactory data collection due to technical issues with the urine collection. The differences in lactulose recovery before and after the intervention will be calculated and compared between the intervention and control groups using *t* tests if the data are normally distributed or the non-parametric Wilcoxon Rank Sum Test if the data are not normally distributed.

Secondary outcomes of interest include linear and ponderal growth, adverse gastrointestinal symptoms, and any side effects due to the interventions. Linear growth will be calculated as the change in length over time, expressed as mm/day. Weight change will be calculated as the change in weight over time, normalized to the enrollment weight, and expressed as g/kg/day. Exploratory analyses of mRNA markers of intestinal inflammation found in the stool will also be conducted as part of our ongoing investigations into identifying novel biomarkers for EED [43, 44].

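### Removing randomised children who become acutely malnourished during follow-up conflicts with the stated intention-to-treat analysis, and the removal is related to outcome

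*Protocol article*

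**What the plan says.** Four places in the protocol article bear on this.

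- **Abstract, Methods/design:** "Intention-to-treat analyses will be used". The primary endpoint is fixed there too: "The primary outcomes of interest will be change in Δ%L from baseline to 8 weeks and to 16 weeks".
- **Anthropometry:** the rule covers weight-for-height Z below –2, MUAC below 12.5 cm, or pitting edema. Its timing is explicit: "During both enrollment and subsequent visits, any child with a weight-for-height" score under the limit (or meeting either other criterion) "will be classified as acutely malnourished and excluded from the study". The next step is also given: "Children excluded due to acute malnutrition will then be enrolled in supplementary or therapeutic feeding programs".
- **Outcomes and sample size:** "Additional children will be enrolled to account for children who drop out or are excluded during the course of the study". The same section lists growth as an outcome: "Secondary outcomes of interest include linear and ponderal growth". It defines the weight measure: "Weight change will be calculated as the change in weight over time, normalized to the enrollment weight, and expressed as g/kg/day".
- **Randomization and blinding:** 250 numbers are pre-assigned, 125 to each group.

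Nowhere does the article say that a child removed after randomisation will still be measured at later visits, or how that child enters the analysis.

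**The concern.** At screening the criteria are an ordinary eligibility rule. At later visits the same rule acts on children who have already been randomised, and it acts on their nutritional course since then. Intention-to-treat needs each randomised child to be followed and analysed in the assigned group; this rule stops follow-up in some of them because of what happened after allocation.

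Two things are at stake. First, the children who remain are no longer the groups that randomisation created. If the supplement improves weight, fewer treated than control children will cross the threshold, and the comparison of those who remain loses more poorly growing children from control. If it worsens weight, the imbalance runs the other way. Second, the later outcomes of these children are not collected, so the gap cannot be closed at analysis. Enrolling more children restores the count but not the comparison.

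**Working it through.** **1. The passages side by side.** Lactulose is tested at weeks 0, 8 and 16 (Lactulose absorption test) and visits are monthly (Study participation). A child removed at week 4 has neither post-baseline primary outcome. A child removed at week 12 lacks week 16. A child who meets the criteria at week 8 may have the week 8 result but not week 16. The sample-size section treats these children as losses, which is how they would appear in the data.

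**2. The plan's own sample size.** Inputs: difference 0.05, alpha 5%, power 90%, 86 per group (Outcomes and sample size). No SD is stated. With n = 2·SD²·(1.960 + 1.282)²/0.05², taking alpha as two-sided, 86 per group implies SD = 0.05·√(86/2)/3.242 = 0.101. As a check, SD 0.10 gives 84.06, rounded up to 85, by this formula, and 85.03, rounded up to 86, by the t-based solution. So 86 is plausible but cannot be verified. The target is 0.05/0.101 ≈ 0.50 SD.

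**3. Power.** The list tolerates a loss of 1 – 86/125 = 31% before a group falls to 86. With 10% of 125 lost, 112.5 remain and power is about 96%. Only if recruitment stopped at 86 per group and 10% of those were lost (about 77 left) would power fall to about 87%, and the plan to enrol extra children makes that unlikely.

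**4. Bias in the primary outcome (assumed rates).** If a share p is removed, and removed children differ from retained ones by a gap g that is equal in both arms, the retained mean equals the full mean minus p·g. The bias in the between-group difference is therefore (p_control – p_treated)·g.

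- 10% v 5% removed, g = 0.10: 0.05 × 0.10 = 0.005, or 10% of 0.05.
- 15% v 5% removed, g = 0.15: 0.10 × 0.15 = 0.015, or 30% of 0.05.

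The second case is extreme. A gap of 0.15 is about 1.5 SD. Under a normal threshold model it needs a correlation of about 0.7–0.8 between lactulose change and the removal criterion. Moving removal from 15% to 5% is also a shift of 1.645 – 1.036 = 0.61 SD in nutritional status, more than the 0.50 SD targeted on lactulose itself.

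A simulation ties the two quantities together: true difference –0.050, SD 0.101, removal more likely when permeability is worse.

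| Removed, control | Correlation | Removed, treated | Difference among those retained |
|---|---|---|---|
| 5% | 0.3 | 3.6% | –0.0492 |
| 10% | 0.3 | 7.6% | –0.0488 |
| 10% | 0.5 | 6.3% | –0.0468 |
| 20% | 0.5 | 13.8% | –0.0452 |

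With zero correlation there is no bias. Over the range examined the effect shrinks by 0% to about 10%.

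**5. Bias in a weight outcome (assumed inputs).** Weight-for-height Z was followed over four monthly visits as a random walk. Assumptions: baseline SD 0.8, SD of total change 0.5, true effect 0.20, removal when Z falls below –2.

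- Baseline mean –0.5: 4.8% of control and 3.0% of treated children removed; the effect becomes about 0.190 (5% lost).
- Baseline mean –0.8: 7.8% v 5.0% removed; the effect becomes about 0.186 (7% lost).

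This uses weight-for-height Z as a stand-in for the plan's g/kg/day and ignores MUAC and edema, which would remove more children.

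**The case against.** The strongest reply is that the article excludes these children from the study without saying that their existing data are discarded. Anthropometry is taken at every visit, so the triggering visit records the failing weight. Growth is defined as a rate and could be computed to that point. The article is condensed, and the handling of withdrawn children is often left to a fuller document. This stands as far as it goes: a reader might infer that these children are deleted from all results, or that harm would be hidden, and the text supports neither. What survives is that outcomes after removal are not planned to be collected, and this is fixed by the article's own rule rather than left open.

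Three further readings are tempting and should be resisted.

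- **That acute malnutrition is a stated consequence of EED.** The Background ties EED to malabsorption and stunting, and the lactulose section reports a correlation with anthropometric growth. A link to wasting is a reasonable inference, not a statement in the protocol. The overlap with ponderal growth is direct, but that is a secondary outcome.
- **That excluded children are swapped for new ones.** With 125 numbers per arm allocated in advance, the extra enrolment is ordinary inflation of the sample size, and every added child is randomised.
- **That the bias is large or power is lost.** The 30% scenario needs implausible inputs, and the 87% power figure ignores the planned extra enrolment.

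It is also fair to object that lactulose testing involves an overnight fast and a four-hour collection. Whether that suits a child just referred for acute malnutrition is a clinical judgement, and the fix must leave it there.

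**Conclusion.** The conflict is real and lies in the current text: post-randomisation exclusion in Anthropometry, with the allowance for it in the sample-size section, cannot be squared with the intention-to-treat statement in the abstract. Removal depends in part on weight-for-height, so it is informative for ponderal growth and may be unequal between arms.

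The size cannot be determined, because the protocol gives no removal rate. On the assumptions above, the bias is about 0–10% of the 0.05 target for lactulose, towards no effect, and about 5–7% for a weight-for-height effect. Neither would by itself overturn the trial. The reason to act is that the rule breaks the declared analysis principle, its effect is unknown in advance, and the lost measurements cannot be recovered later.

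**What to change.** Reconcile the three passages so that meeting the criteria after randomisation leads to referral and care exactly as the protocol already has them, but not to removal from follow-up or analysis. In particular:

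- Keep all data up to and including the triggering visit.
- Continue the scheduled anthropometry.
- Obtain the week 8 and week 16 lactulose outcomes where the treating clinicians consider it appropriate.
- Analyse every child in the assigned group, with any missing outcomes handled by a pre-specified method.
- Report acute malnutrition during follow-up by arm.
- Show the analysis without these children only as a sensitivity analysis.

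The cost is an amendment and a few extra measurements. Recruitment and follow-up are described as ongoing, anthropometry is already monthly, and urine is to be assayed together at the end, so the change remains practicable. The downside is that feeding-programme care may dilute the supplement's effect in the referred children; the sensitivity analysis will show how far their inclusion alters the result.

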### Lactulose absorption test

The lactulose absorption test is a modification of the dual-sugar absorption test [54] and will be used as a measure of gut integrity. This test has previously been correlated with histological changes in the small bowel [55], severity of diarrhea [56], micronutrient status [57, 58], metabolic abnormalities [59], and anthropometric growth [60]. This test involves the oral ingestion of a sugar solution with subsequent urine collection to determine the degree to which the sugars are absorbed within the intestine and enter the systemic circulation.

Lactulose is a large disaccharide that cannot cross these tight junctions, and can only traverse the intestinal epithelium in large quantities if there are significant disruptions [61]. The percentage of ingested lactulose excreted in the urine is a measure of intestinal mucosal permeability, with a higher percentage signifying increased intestinal permeability.

Children will be asked to take no food (water and breast milk are permitted) after 10 pm on the evening before each sample collection date (weeks 0, 8, and 16). Each child will meet at the community meeting point in the village at 6 am with the research team. Each child then will drink 20 mL of a solution containing 5 g lactulose. Children who spit up or vomit the solution will return on a subsequent day to try again. Adhesive urine bags will then be placed on the child’s perineum to capture each urination. Once a child has voided any quantity of urine, the bag will be removed and the urine will be transferred to a clean container specific to the child, and then a new urine bag will be placed on the child. Thimerosol (10 mg) dissolved in 20 μL of water will be added to each child’s urine container to prevent bacterial degradation of the sugars. Caretakers and children are told to avoid breastfeeding, and will remain at the community meeting point for the next 4 h. Four hours after drinking the sugar solution, children will be encouraged to void and complete the urine collection, after which the total volume of urine will be quantified and aliquots portioned into cryovials. These samples will be stored in liquid nitrogen tanks in the field and then stored in –80 °C freezers until they can be transported back to the United States. The urinary concentration of lactulose will be measured by high-pressure liquid chromatography (HPLC) as described previously [62]. The total excretion of lactulose will be determined by multiplying this concentration by the total volume of urine.

### Data management and analysis

Clinical data focusing on demographic and anthropometric values will be collected on standardized forms by field workers. Data will be double-entered into a password-protected Microsoft Access database by research assistants blinded to the intervention assignment. All discrepancies will be resolved by examination of the original forms and discussion with the relevant field workers. After entering all data and resolving inconsistencies, the data set will be locked. For anthropometric values, comparisons will be made between the lactoferrin-lysozyme mixture and the control rice flour groups. Fisher’s exact test will generally be used to compare discrete parameters, and Student’s *t* test will be used for continuous parameters. A difference with *P* < 0.05 will be considered statistically significant. These statistical methods will also be used for all clinical data and EED measures.

All trial data, including personal information, will be kept in password-protected encrypted computer databases on password-protected computers. Paper records will be kept in locked file cabinets and the research team’s headquarters in locked buildings. Given the relatively short duration of the study and the need to analyze all urine concentrations simultaneously at the end of the study, no interim analyses are planned and no stopping guidelines have been established. The full protocol, participant-level dataset, and details of all statistical analyses will be made available to any interested parties after the conclusion of the trial by contacting the principal investigators.

## Discussion

Malnutrition and chronic enteric infections are closely intertwined global health problems. Ever since the 1960s, it has been known that the two in concert cause long-term growth stunting and impaired cognitive development [63]. Since then, studies have quantified the effect of enteric infections and have found that diarrheal episodes in the first 2 years of life can account for 25% or more of stunting [64], and newer research suggests a link to non-communicable diseases such as cardiovascular disease and type II diabetes [65]. Central to the treatment of stunting will be interventions targeted against EED. Past studies have tested pharmacologic interventions against EED, but effects have been minimal [66].

Breast milk provides a number of benefits for developing infants, including the provision of energy, gut maturation, and immunologic functions [67]. Though the use breastfeeding as an intervention to treat undernutrition has shown only modest reduction in stunting, it decreases mortality rates significantly [2]. Thus, use of breast milk components in supplements may be useful in the prevention and/or treatment of EED. Lactoferrin and lysozyme are of particular interest as they are both present in substantial concentrations within breast milk, and increase substantially in concentration during lactation [68]. Their antimicrobial properties have been demonstrated in vitro [22] and in vivo [34], along with potential benefits to intestinal health [34], and it is our hope that their use as interventions may help attenuate EED.

One limitation of this study is the lack of complete blinding. The control and experimental interventions have physical differences that may be noticeable to discerning caregivers, who may subsequently exchange their interventions with others. We believe that this will be an unlikely occurrence since past research in this area of Malawi did not demonstrate any evidence of sharing or trading for food [69] or pharmacological [70] interventions. Extensive community education of local officials, caregivers, and workers will stress the importance of complying with the assigned interventions, which should decrease the occurrence of sharing. Preliminary acceptability studies showed that children liked the interventions equally, which should also decrease the motivation for trading. There is also potential for sharing of the interventions with other family members, but this is relatively unlikely as the amount administered is unlikely to be satisfying to hungry family members.

## Trial status

Recruitment and follow-up of trial participants is ongoing.

## Abbreviations

EED: Environmental enteric dysfunction
GRAS: Generally Regarded as Safe
HPLC: High-pressure liquid chromatography
HSA: Health Surveillance Assistant
MUAC: Mid-upper arm circumference
SPIRIT: Standard Protocol Items, Recommendations for Interventional Trials
WHO: World Health Organization
